**S1: Protocol of planned analysis submitted to Hamilton Integrated Research Ethics Board**

**Background and study relevance.**

Spirometry is an effort-dependent test, which measures lung capacity, an important indicator of lung health. This information is pivotal in the diagnosis of respiratory diseases. However, lung capacity alone has also been shown to be an important and independent predictor of all-cause mortality and cardiovascular events (CVD)[1-5]. Furthermore, there is emerging data linking lung function to the development of other chronic diseases such as strokes, diabetes mellitus, cancers and renal diseases [6,7]. This suggests that lung capacity may serve as a broad indicator of general health and survival and not just lung health. Such a measure can be useful in the risk stratification of premature death, CVD events and development of certain chronic diseases. Furthermore, the underlying mechanistic links for these associations are not well understood and have not been extensively examined.

We propose to utilise the CLSA spirometry data, which is the largest spirometry dataset collected to date from the Canadian population with sufficient representative numbers for the ages of 45 to 85 years, to examine the prevalence and phenotypes of impaired spirometric lung function in the general population and how it relates to symptoms, general health and functional status.

**Relevance:** These findings will provide a better understanding on the broader implications of spirometry and aging. It addresses a number of gaps in knowledge regarding the relationship between lung capacity (spirometry), morbidity, physical impairment and disability.

**Study Objectives/ Hypothesis:** We hypothesized that spirometry is a simple and sensitive measure of a highly complex integrative process involving the neuromuscular axis, muscle strength, chest-wall mechanics and lung mechanics. Each component needs to operate efficiently individually and together to provide the optimal conditions for oxygen extraction and delivery to meet the body’s metabolic demand. However, the aging process and other systemic pathological conditions can adversely impact on the structural integrity and function of any one or more of these individual components, leading to alterations in the overall measured ventilatory capacity parameters on spirometry. We postulate that in certain individuals, who experience accelerated aging, a process that causes excessive structural and physiological decline to one or more of these components, can lead to excessive decline in lung capacity than otherwise be expected for normal aging. At the same time, the accelerated aging process increase the risks for mortality and development of chronic diseases. Therefore, spirometry may serve as an important marker of accelerated aging, and allows the identification of individuals who are vulnerable to excessive morbidity and mortality. The Canadian Longitudinal Study on Aging (CLSA) cross-sectional baseline data can provide further insights into this proposed mechanism and the broader implications of impaired lung function with aging.

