**Study design, methodology, and data analysis proposed:** Data from the 30,000 participants with spirometry measurements will be included in this proposal. Listed below are the steps that will be undertaken for validation of data quality and statistical analysis. (1) Validation of spirometry quality: As recommended by international guidelines, the quality of the spirometry needs to be individually verified by inspecting the spirographs generated following each effort [9]. If available, these will be inspected to ensure they meet the quality criteria for acceptability and reproducibility by international guidelines. For the higher grade measurements (as assessed by the spirometer software, grades A-C), 30% will be randomly selected for manual inspection by a trained personnel in spirometry reading. An agreement rate between the assessments by manual inspection and the spirometer of >90% will be considered acceptable. For the lower grades (grades D-F), all measurements will be inspected to select out the acceptable values measured with each effort. If spirographs are not available then plausibility of the data will be determined based on the participants age, sex, height and ethnicity. In this case, only grades A-C measurements will be used. Based on the published literature, it is anticipated that up to 30% of spirometry performed outside pulmonary function laboratory setting are considered suboptimal and excluded [11]. Therefore, we anticipate that the final sample size to be approximately 20,000 participants. Those failing to reach international guidelines standards will be explored to see if the same consequences apply i.e. are the standards excessively stringent. This issue is important to address, since the higher standards/guidelines currently being followed may be a major reason why spirometry is not being widely adopted and implemented in the community. Perhaps less stringent quality criteria may be more appropriate if the outcome for its intended use i.e. assessment of morbidity and mortality is the same. (2) Establishing age-, sex-appropriate reference values: A non-linear multiplicative regression model, which adjusts for height, age, sex and ethnicity that we have derived and validated in another large population-based study, PURE [12], will be used to generate reference equations for the CLSA population. These equations will provide the predicted/expected values for the FEV1, FVC and FEV1/FVC according to the height, age, sex and ethnic distribution in the CLSA cohort. The measured FEV1, FVC and FEV1/FVC for each participant will be compared to their predicted values and expressed as a percentage of the predicted (i.e. %pred = measured/predicted x 100). These %pred values provide an indication of the impairment level relative to the overall adjusted population average. A Z-score will then be calculated for each %pred value. The characteristics of participants with a Z-score of 0 or higher (i.e. population mean and higher) will be examined to determine the appropriate selection criteria that enables the selection of participants with the highest adjusted spirometric values in the population. The %pred values generated with this method will then be compared to the traditional selection criteria (i.e. based on self-reported never-smoking and no comorbidities). The relationship between the %pred derived from each method (population-average reference vs healthy cohort-reference), to symptoms, physical impairment and healthcare utilization will be examine to provide face validity to each method. (3) Establishing clinically-meaningful thresholds for diagnosing respiratory impairment that relates to symptoms, physical impairment and health care utilization. Hierarchical logistic regression will be used to establish the adjusted odds ratios (ORs) for symptoms (COPD and heart questionnaires), exercise tolerance (physical activity, 4 minute walk test), functional impairment (IAL, ADL, functional status), health resource utilization (receiving formal and informal care, hospitalization, medication use), across the Z score categories of the ‘population-average reference’. This will provide the magnitude of the relative risks of morbidity associated with each level of lung function impairment (%predFEV1, %predFVC) below the population average; and the relationship across the ORs across different severity of lung function impairment (i.e. linear trend in ORs or other pattern). By examining the relationship between the ORs for morbidity by lung function level will help determine the appropriate threshold to define impairment (4) Defining the different spirometric phenotypes and their relationship to co-morbidities. Spirometric impairment phenotypes will be examined using the threshold established from objective 3 above together with the FEV1/FVC ratio threshold for obstructive (i.e. FEV1/FVC <0.7) vs non-obstructive (>=0.70) phenotypes. Hierarchical logistic regression will be used to examine for any relationship between spirometric phenotypes and self-reported diagnoses of cardiovascular, strokes, neurological, auto-immune/ connective tissue diseases, osteoporosis, osteoarthritis, falls, medication use, hospital utilization. This exploratory analysis will provide insight into the relationship between multi-morbidity and clustering of certain co-morbidities to spirometric impairment phenotypes and the possible underlying mechanistic links/pathways.

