
**Sample size justification:** With the population-average reference method all high quality acceptable spirometry will be included, which is anticipated to be 20,000 participants. For the healthy-cohort reference methods, it is anticipated that 30% will be excluded due to smoking, symptoms or self-reported comorbidities giving an estimated sample size of 16,000. This sample is at least 10 fold larger than the present Canadian reference values [10] and therefore should provide enough power and robustness to our findings.

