**Amendments to the protocol:**

December 2017: Some of the planned outcome variables such as healthcare utilization, medication use and activities of daily living were not available at the time and therefore were omitted from the analyses.

October 2019: Following the recommendations from ATS, which endorsed the use of the Global Lung Function Initiative (GLI) predictive values for the interpretation of FEV1 and FVC, we elected to remove objective 1 which was to establish our own predictive values using the CLSA spirometry data. Instead we used the GLI predictive values to interpret and grade the severity of FEV_1_.

January 2020: we decided to report on the graded relationship between FEV1 categories with outcomes rather than establishing thresholds since the relationship we observed was continuous throughout the range of the FEV1.

November 2021: Unadjusted analyses were conducted as requested by reviewers from PLOS Medicine and analyses on the FVC

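### Spirometry is to be read as a marker of general health, but the graded FEV1 analysis pools smokers and people with lung disease, so for symptoms and exercise tolerance lung disease alone could produce the gradient

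*Protocol*

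**What the plan says.** The background section of the protocol states that "lung capacity may serve as a broad indicator of general health and survival and not just lung health". The section on objectives and hypothesis carries the idea forward: "spirometry may serve as an important marker of accelerated aging".

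The analysed population is set in the study design and data analysis section: "Data from the 30,000 participants with spirometry measurements will be included in this proposal". The only exclusion that reduces it is test quality: "it is anticipated that up to 30% of spirometry performed outside pulmonary function laboratory setting are considered suboptimal and excluded". The sample size section confirms this for the population-average set: "all high quality acceptable spirometry will be included, which is anticipated to be 20,000 participants".

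Step (3) estimates "adjusted odds ratios (ORs) for symptoms (COPD and heart questionnaires), exercise tolerance (physical activity, 4 minute walk test"), along with functional impairment and use of health resources, across categories of lung function in that pooled set. The odds ratios are called adjusted; the covariates are not named.

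Smoking and disease status are used for selection only in step (2), where reference values from the population are compared with those from the "traditional selection criteria (i.e. based on self-reported never-smoking and no comorbidities"). That step served objective 1. In October 2019, "we elected to remove objective 1 which was to establish our own predictive values using the CLSA spirometry data", and GLI values took their place.

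Two other amendments matter. In December 2017, outcomes such as health-care utilization, medication use and activities of daily living were omitted because they were not available. In January 2020 the aim became to report a graded relation of FEV1 categories with outcomes instead of setting thresholds.

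Step (4) splits impairment by FEV1/FVC below 0.7 versus 0.70 or above, and relates the phenotypes to self-reported non-respiratory diagnoses such as cardiovascular disease, stroke and osteoarthritis.

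**The concern.** To say that spirometry carries information beyond lung health, the analysis has to separate general decline from primary lung disease. The graded analysis does not do so as written. Airway disease lowers FEV1, and it also causes the symptoms a COPD questionnaire records and limits exercise. A stepwise rise in odds ratios as FEV1 falls is therefore expected from lung disease alone, and that is the pattern the January 2020 amendment chooses to report. The loss of several non-symptom outcomes in December 2017 gives symptoms and exercise more weight.

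At stake is the interpretation. A reader shown a pooled gradient in these outcomes could not tell a marker of general health from a marker of lung disease.

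**Working it through.** **The plan's own figures.** No alpha, power or effect size is given, so there is no sample-size formula to reproduce. The counts can be checked:
- 30,000 × 0.70 = 21,000, against a stated figure of approximately 20,000.
- Healthy-cohort set after a 30% exclusion: 20,000 × 0.70 = 14,000, or 21,000 × 0.70 = 14,700. The sample size section states 16,000, which implies 1 − 16,000/20,000 = 20% excluded (23.8% from 21,000). The 30% and the 16,000 do not agree.

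**Hand illustration (all inputs assumed).** Low FEV1 has no effect of its own; the outcome depends only on airway disease.
- b: outcome prevalence without airway disease, 0.10 to 0.20.
- q: prevalence with airway disease, from an odds ratio of 3 or 4.
- s: share with airway disease among people with low FEV1, 0.3 to 0.6.
- t: the same share among people with normal FEV1.
- Pooled OR = odds(s·q + (1−s)·b) / odds(t·q + (1−t)·b).

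With t = 0:
- Low end (b = 0.20, OR 3, s = 0.3): q = 0.75/1.75 = 0.4286; p = 0.3 × 0.4286 + 0.7 × 0.20 = 0.2686; odds 0.3672; OR = 0.3672/0.25 = 1.47.
- High end (b = 0.10, OR 4, s = 0.6): q = 0.4444/1.4444 = 0.3077; p = 0.6 × 0.3077 + 0.4 × 0.10 = 0.2246; odds 0.2897; OR = 0.2897/0.1111 = 2.61.

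Setting t = 0 is generous to the concern. More realistic values shrink the range:

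| t | Pooled OR |
|---|---|
| 0 | 1.47 to 2.61 |
| 5% | 1.37 to 2.33 |
| 10% | 1.28 to 2.11 |
| 15% | 1.20 to 1.92 |

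**Simulation (all inputs assumed).** 20,000 people, 30 runs per scenario; 50% ever-smokers; lung disease in smokers/never-smokers of 10%/4%, 20%/6% or 30%/8%. Disease lowers the FEV1 Z-score by 1.5 and triples the odds of the outcome (15% at baseline); 70% of it is obstructive. FEV1 has no direct effect. Mean OR per 1 Z lower FEV1:

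| Analysis | 10%/4% | 20%/6% | 30%/8% |
|---|---|---|---|
| Pooled, unadjusted | 1.13 | 1.20 | 1.24 |
| Pooled, adjusted for smoking | 1.13 | 1.19 | 1.23 |
| Obstructive lung disease removed | 1.05 | 1.09 | 1.13 |
| All lung disease removed | 1.00 | 1.00 | 1.00 |

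In both pooled rows the lower confidence limit exceeded 1 in every run. The unadjusted category odds ratios (against Z of 0 or above) rose in steps: 1.07, 1.27, 1.88 in the first scenario and 1.18, 1.60, 2.32 in the last. A pooled model adjusted for lung disease as well as smoking gave an odds ratio no higher than about 1.01. For an outcome driven only by smoking, the pooled OR was 1.01 to 1.03, and null once smoking was in the model.

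**Imperfect reporting.** If only 40% to 60% of lung disease is self-reported (assumed), never-smokers without reported disease still show a false OR of about 1.04 to 1.10.

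**The case against.** The strongest reply has four parts.

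*The objectives do not ask this question.* They concern reference values, thresholds, and prevalence and phenotypes, and the background's stated aim is a general-population description. The hypothesis also counts lung mechanics as one component of what spirometry measures. So pooling suits the descriptive aim, and this stands. But the hypothesis also wants the result read as accelerated aging, and that reading is where the pooled analysis falls short.

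*The remedy belongs in a statistical analysis plan, which is not shown.* Unnamed covariates are indeed no finding, and a restricted analysis may exist elsewhere; the last amendment entry also breaks off in the text available. But the protocol itself fixes both the pooled population and the intended reading, and these do not match.

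*The plan has its own safeguards.* The FEV1/FVC split and the non-respiratory diagnoses in step (4), and the heart questionnaire in step (3), all help. A reader might infer that the general-health question stays unanswered whatever the odds ratios show. The document does not support that: a relation between non-obstructive impairment and stroke or osteoarthritis would be informative. The safeguards are nonetheless partial. They do not cover the graded analysis, and they leave in smokers and non-obstructive lung disease.

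*Adjustment could solve it.* A reader might infer that covariates cannot help. They can: conditioning on lung disease removes the false gradient in the simulation. Smoking alone does not.

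**Conclusion.** The point holds as a limit on interpretation. For COPD symptoms and exercise tolerance, the pooled graded analysis cannot by itself separate general health from lung disease. It is weaker for outcomes such as stroke or osteoarthritis, though some of these may share smoking as a cause.

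Only the direction of the false gradient is claimed. The figures of 1.20 to 2.61 for low versus normal FEV1, and 1.13 to 1.24 per Z, rest wholly on assumed prevalences and effects, and the document supplies none of these.

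Two further inferences go too far. One is that the restricted group is known to be large because the plan expects to exclude 30%: that exclusion uses a different rule (smoking, symptoms or comorbidities), and it conflicts with the stated 16,000. The other is that a gradient retained in the restricted group would settle the matter: self-report misses undiagnosed disease, which can leave a small gradient behind.

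**What to change.** Add a sensitivity analysis, labelled as such because the protocol has already been amended up to November 2021:

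1. Repeat the graded FEV1 (and FVC) models in never-smokers with no self-reported asthma, COPD or other lung disease and FEV1/FVC of at least 0.70. Do not exclude on symptoms or non-respiratory comorbidity, since these are the outcomes.
2. Show it beside the whole-cohort result and a whole-cohort model adjusted for lung disease and smoking.
3. Report respiratory symptoms separately from general-health outcomes.
4. Word the conclusion about general health according to whether the gradient is retained in the restricted set, and name undiagnosed lung disease as a residual explanation.

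The cost is a few extra models and wider intervals. The size of the restricted set cannot be derived from the sample size section. On the simulation's assumptions it would be 20,000 × 0.5 × (0.92 to 0.96) = 9,200 to 9,600 before the FEV1/FVC condition. The analysis also needs self-reported respiratory diagnoses, which the list in step (4) does not name. Separately, the 30% and the 16,000 in the sample size section should be reconciled.

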**The objectives for this proposal are:**

1. To establish age- and sex- appropriate spirometric reference values using the large CLSA population-based spirometric database that is representative in numbers for the age groups of 45- 85 years and the current demographics of the Canadian population.

2. To derive appropriate thresholds for spirometric impairment and severity that relates to co-morbidity, and physical impairment.

3. To examine the prevalence of spirometry impairment and the phenotypes (obstructive versus non-obstructive) and how the phenotype relates to morbidity.

**Study design, methodology, and data analysis proposed:** Data from the 30,000 participants with spirometry measurements will be included in this proposal. Listed below are the steps that will be undertaken for validation of data quality and statistical analysis. (1) Validation of spirometry quality: As recommended by international guidelines, the quality of the spirometry needs to be individually verified by inspecting the spirographs generated following each effort [9]. If available, these will be inspected to ensure they meet the quality criteria for acceptability and reproducibility by international guidelines. For the higher grade measurements (as assessed by the spirometer software, grades A-C), 30% will be randomly selected for manual inspection by a trained personnel in spirometry reading. An agreement rate between the assessments by manual inspection and the spirometer of >90% will be considered acceptable. For the lower grades (grades D-F), all measurements will be inspected to select out the acceptable values measured with each effort. If spirographs are not available then plausibility of the data will be determined based on the participants age, sex, height and ethnicity. In this case, only grades A-C measurements will be used. Based on the published literature, it is anticipated that up to 30% of spirometry performed outside pulmonary function laboratory setting are considered suboptimal and excluded [11]. Therefore, we anticipate that the final sample size to be approximately 20,000 participants. Those failing to reach international guidelines standards will be explored to see if the same consequences apply i.e. are the standards excessively stringent. This issue is important to address, since the higher standards/guidelines currently being followed may be a major reason why spirometry is not being widely adopted and implemented in the community. Perhaps less stringent quality criteria may be more appropriate if the outcome for its intended use i.e. assessment of morbidity and mortality is the same. (2) Establishing age-, sex-appropriate reference values: A non-linear multiplicative regression model, which adjusts for height, age, sex and ethnicity that we have derived and validated in another large population-based study, PURE [12], will be used to generate reference equations for the CLSA population. These equations will provide the predicted/expected values for the FEV1, FVC and FEV1/FVC according to the height, age, sex and ethnic distribution in the CLSA cohort. The measured FEV1, FVC and FEV1/FVC for each participant will be compared to their predicted values and expressed as a percentage of the predicted (i.e. %pred = measured/predicted x 100). These %pred values provide an indication of the impairment level relative to the overall adjusted population average. A Z-score will then be calculated for each %pred value. The characteristics of participants with a Z-score of 0 or higher (i.e. population mean and higher) will be examined to determine the appropriate selection criteria that enables the selection of participants with the highest adjusted spirometric values in the population. The %pred values generated with this method will then be compared to the traditional selection criteria (i.e. based on self-reported never-smoking and no comorbidities). The relationship between the %pred derived from each method (population-average reference vs healthy cohort-reference), to symptoms, physical impairment and healthcare utilization will be examine to provide face validity to each method. (3) Establishing clinically-meaningful thresholds for diagnosing respiratory impairment that relates to symptoms, physical impairment and health care utilization. Hierarchical logistic regression will be used to establish the adjusted odds ratios (ORs) for symptoms (COPD and heart questionnaires), exercise tolerance (physical activity, 4 minute walk test), functional impairment (IAL, ADL, functional status), health resource utilization (receiving formal and informal care, hospitalization, medication use), across the Z score categories of the ‘population-average reference’. This will provide the magnitude of the relative risks of morbidity associated with each level of lung function impairment (%predFEV1, %predFVC) below the population average; and the relationship across the ORs across different severity of lung function impairment (i.e. linear trend in ORs or other pattern). By examining the relationship between the ORs for morbidity by lung function level will help determine the appropriate threshold to define impairment (4) Defining the different spirometric phenotypes and their relationship to co-morbidities. Spirometric impairment phenotypes will be examined using the threshold established from objective 3 above together with the FEV1/FVC ratio threshold for obstructive (i.e. FEV1/FVC <0.7) vs non-obstructive (>=0.70) phenotypes. Hierarchical logistic regression will be used to examine for any relationship between spirometric phenotypes and self-reported diagnoses of cardiovascular, strokes, neurological, auto-immune/ connective tissue diseases, osteoporosis, osteoarthritis, falls, medication use, hospital utilization. This exploratory analysis will provide insight into the relationship between multi-morbidity and clustering of certain co-morbidities to spirometric impairment phenotypes and the possible underlying mechanistic links/pathways.

**Sample size justification:** With the population-average reference method all high quality acceptable spirometry will be included, which is anticipated to be 20,000 participants. For the healthy-cohort reference methods, it is anticipated that 30% will be excluded due to smoking, symptoms or self-reported comorbidities giving an estimated sample size of 16,000. This sample is at least 10 fold larger than the present Canadian reference values [10] and therefore should provide enough power and robustness to our findings.

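### Step (3) reads adjusted odds ratios from cross-sectional data as relative risks; they are prevalence odds ratios and exceed the prevalence ratio wherever outcomes are not rare

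*Protocol*

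**What the plan says.** The protocol section on study design, methodology and data analysis, step (3), fixes the effect measure: "Hierarchical logistic regression will be used to establish the adjusted odds ratios (ORs) for symptoms". The same analysis covers exercise tolerance, functional impairment and use of health resources, across Z-score categories of lung function. The next sentence fixes how the result is to be read: "This will provide the magnitude of the relative risks of morbidity associated with each level of lung function impairment". Step (3) then plans to look at the pattern of ORs across severity, including whether the trend is linear, and to use it to set a cut-off: "By examining the relationship between the ORs for morbidity by lung function level will help determine the appropriate threshold to define impairment".

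The section on study objectives and hypothesis states the design: "The Canadian Longitudinal Study on Aging (CLSA) cross-sectional baseline data can provide further insights into this proposed mechanism".

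No prevalence is given for any single outcome. The nearest figure is in the sample size justification, where "it is anticipated that 30% will be excluded due to smoking, symptoms or self-reported comorbidities". That is a composite which includes smoking.

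Three entries under Amendments to the protocol bear on the point:

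- December 2017 drops outcomes: "Some of the planned outcome variables such as healthcare utilization, medication use and activities of daily living were not available".
- October 2019 moves to the Global Lung Function Initiative predicted values.
- January 2020 replaces threshold-setting with a graded relationship between FEV1 categories and outcomes.

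None of them revisits the reading of ORs as relative risks. The protocol states no rare-outcome condition and plans no prevalence or risk ratio.

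**The concern.** The sentence makes a claim about magnitude, and magnitude is what an OR does not share with a relative risk unless the outcome is rare. Two separate things are wrong with it.

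1. **The name of the quantity.** With one cross-section there is no follow-up in which morbidity could develop. What can be compared is how often an outcome is present, so the OR is a prevalence odds ratio. Risk is the wrong word at any prevalence.
2. **The size.** An OR above 1 is always larger than the matching prevalence ratio. The gap grows with the prevalence in the reference category and with the OR itself, so it is widest in the most impaired categories.

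Since January 2020 the graded relationship is the result to be reported. If its ORs are read as relative risks, readers would take a doubling or tripling of the odds for a doubling or tripling of the frequency of morbidity. The gradient would seem steeper than the prevalences show, by an amount nobody can judge without the prevalences.

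**Working it through.** **Inputs.** From the protocol: the measure is an adjusted OR (step 3), it is read as a relative risk (step 3), and the data are cross-sectional (study objectives and hypothesis). The protocol states no OR, relative risk or outcome prevalence on this point, so there is no figure of its own to reproduce. The values of p0 and OR below are assumptions, shown over a range that includes rare outcomes.

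**Formulas.** Let p0 be the outcome prevalence in the reference category and p1 that in an impaired category.

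- p1 = OR × p0 / (1 − p0 + OR × p0)
- Prevalence ratio: PR = p1/p0 = OR / (1 + p0 × (OR − 1))
- Overstatement if the OR is read as a ratio of frequencies: OR/PR − 1 = p0 × (OR − 1)

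These are exact for a crude two-group comparison. For covariate-adjusted ORs from a hierarchical model they are an approximation.

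**Example.** With OR = 3 and p0 = 30%, PR = 3 / (1 + 0.30 × 2) = 3/1.6 = 1.875. The overstatement is 0.30 × 2 = 60%. The excess is read as 200% when it is 87.5%.

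**Range.**

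| Assumed p0 | PR behind OR 2 | Overstated by | PR behind OR 3 | Overstated by |
|---|---|---|---|---|
| 1% | 1.98 | 1% | 2.94 | 2% |
| 5% | 1.90 | 5% | 2.73 | 10% |
| 10% | 1.82 | 10% | 2.50 | 20% |
| 20% | 1.67 | 20% | 2.14 | 40% |
| 30% | 1.54 | 30% | 1.88 | 60% |
| 50% | 1.33 | 50% | 1.50 | 100% |

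**Where the gap reaches 10%.** Setting p0 × (OR − 1) = 0.10 gives p0 = 0.10/(OR − 1). That is 20% for OR 1.5, 10% for OR 2, 5% for OR 3 and 3.3% for OR 4.

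**Effect on a gradient.** Assume the OR rises by a factor of 1.5 per category step.

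| Steps below reference | OR | PR at p0 = 5% | PR at p0 = 20% | PR at p0 = 30% |
|---|---|---|---|---|
| 1 | 1.50 | 1.46 | 1.36 | 1.30 |
| 2 | 2.25 | 2.12 | 1.80 | 1.64 |
| 3 | 3.38 | 3.02 | 2.29 | 1.97 |
| 4 | 5.06 | 4.21 | 2.79 | 2.28 |

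The order of the categories is the same on both scales. The steepness is not: at p0 = 20% the most impaired category shows an OR of 5.06 against a prevalence ratio of 2.79.

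**The case against.** The strongest reply is that this is one loose phrase. The OR is a valid measure of association for prevalent outcomes, step (3) openly analyses trends in ORs, and logistic regression is a standard choice. The phrase also sits in a step written for Z-score categories and threshold-setting, which the 2019 and 2020 amendments replaced. Part of this stands: the model is not at fault, and ORs need not be dropped or demoted. But the amendments changed the reference values, the outcomes and the threshold aim, and left the interpretation as it was. The graded relationship that remains still depends on how its effect sizes are read.

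A reader might infer several stronger points that the protocol does not support.

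- **That the outcomes are common, so the effects are overstated.** No outcome prevalence is given, and the 30% composite includes smoking. High prevalence is plausible for symptoms or limited exercise tolerance at ages 45 to 85, but it is an assumption. At 1% prevalence the gap is only 1–2% for ORs of 2 to 3. For a walk test, prevalence depends on the cut-off chosen.
- **That the cross-sectional design inflates the estimate.** It does not. It makes risk the wrong word; the numerical gap comes from outcome frequency.
- **That healthcare use and activities of daily living are among the affected results.** Those outcomes were omitted in December 2017.
- **That outcomes would be ranked wrongly.** The protocol plans no ranking. Prevalence ratios depend on prevalence too, since they cannot exceed 1/p0: the ceiling is 2.5 at p0 = 40% and 10 at p0 = 10%.
- **That the direction of the gradient is in doubt.** With a common reference category, PR rises whenever OR rises, so only the steepness changes.

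**Conclusion.** The point holds as a fault of interpretation. The protocol states that its ORs give the magnitude of relative risks, the data allow only prevalence comparisons, and nothing in the protocol limits the statement to rare outcomes or corrects it later.

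That an OR above 1 exceeds the prevalence ratio is certain. By how much is unknown until the outcome prevalences are shown. Under the assumed values above, the gap is negligible at about 1% prevalence and material from about 10% upwards for an OR of 2, or from about 5% for an OR of 3. The figures carry over only approximately to the adjusted, hierarchical ORs that are planned. The existence and direction of an association are not affected; what may be said about its size and steepness is. The correction should be made.

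**What to change.** 1. In step (3), replace the term relative risks with prevalence odds ratios, and carry that into the reporting of the graded FEV1 relationship.
2. Report the prevalence of each retained outcome by FEV1 category, including the reference category, so that readers can see where the OR and the prevalence ratio part company.
3. Alongside the ORs, give adjusted prevalence ratios or prevalence differences with confidence intervals. Marginal standardisation from the planned logistic model does this without changing the model. Modified Poisson regression with robust standard errors, clustered where the model is hierarchical, is an alternative.

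No new data are needed. The cost is a wording change, one more table and a few lines of code. The drawback is that ratios on the prevalence scale will look smaller than the ORs, most visibly in the most impaired categories.
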